## Abstract

**Background:**

Individuals with schizophrenia experience significantly higher rates of chronic physical health conditions, driving a 20-year reduction in life expectancy. Poor diet quality is a key modifiable risk factor; however, owing to side-effects of antipsychotic medication, cognitive challenges and food insecurity, standard dietary counselling may not be sufficient for this population group.

**Aim:**

To evaluate the feasibility, acceptability and preliminary effectiveness of two dietary interventions – pre-prepared meals and meal kits – for individuals with schizophrenia.

**Method:**

The Schizophrenia, Nutrition and Choices in Kilojoules (SNaCK) study is a 12-week, three-arm, cross-over, randomised controlled trial. Eighteen participants aged 18–64 years diagnosed with schizophrenia or schizoaffective disorder will be recruited from community mental health services in Australia. Participants will be randomised to receive pre-prepared meals, meal kits or a supermarket voucher as a control, crossing-over at the end of weeks 4 and 8, so that all participants experience all three study arms. Primary outcomes include feasibility (recruitment rate and retention, number of days participants use pre-prepared meals or meal kits, adherence to meals as prescribed, difficulty in meal preparation and meal wastage) and acceptability (meal provision preference ranking and implementation) of the nutrition interventions. Secondary outcomes include the effects of the intervention on metabolic syndrome components, dietary intake, quality of life and food security measures.

**Conclusions:**

Feasible, acceptable and effective dietary interventions for people with schizophrenia are urgently needed. Findings from this trial will inform future larger randomised controlled trials that have the potential to influence policy and improve health outcomes for this vulnerable population.

People living with schizophrenia experience chronic physical health conditions at rates 2–5 times higher than the general population,^
1
^ with cardiovascular disease making the greatest contribution to the 10- to 16-year gap in life expectancy.^
2
^ Drivers of these disparities can be wide-ranging. A key modifiable risk factor is poor diet, frequently characterised in this population group by excessive dietary intake of poor nutritional quality.^
3
^ Side-effects of antipsychotic medication (and other psychotropics) often include increased hunger,^
4
^ food cravings and disordered eating behaviours^
5
^ such as binge eating, while also potentially having sedative effects.^
6
^ Cognitive impacts of the illness, such as impairments in executive functioning, facilitate eating disinhibition^
7
^ and may affect a person’s knowledge, confidence, skills and motivation to plan and prepare nutritious meals.^
8
^ Further, food access is frequently an issue, given the limited income of many people living with schizophrenia.^
9
^

Lifestyle interventions are considered an effective means of improving metabolic health in this population group; however, without adequate resources, they are often affected by uptake, adherence and attrition issues, particularly in people who experience more severe clinical symptoms.^
10
^ Pre-prepared meals and meal kits require less effort and planning compared with the complex cognitive process of planning, shopping and preparing a meal and may enable and empower people with schizophrenia to independently prepare and consume healthier meals. A recent pilot study (*n* = 24), including people with depression and food insecurity who were provided with a weekly box of fresh fruit and vegetables, found that the intervention was acceptable to participants, with two-thirds of participants showing improvements in depression at project end.^
11
^ To our knowledge, the feasibility and impact of providing healthy pre-prepared meals or meal kits has not previously been investigated in a population of individuals living with mental illness.

Here, we aimed to test the feasibility, acceptability and preliminary efficacy of dietary interventions using pre-prepared meals and meal kits among people living with schizophrenia.

## Method

### Study design

The SNaCK study is a 12-week, three-arm, cross-over, three-arm randomised controlled trial (RCT) (4 weeks per study arm) using a mixed-methods evaluation to test the feasibility, acceptability and preliminary efficacy of two dietary interventions compared with an active control condition among people with schizophrenia or schizoaffective disorder (Fig. 1). This trial was registered with the Australian and New Zealand Clinical Trials Registry (trial ID: ACTRN12623001024639) and reported according to the SPIRIT-Outcomes 2022 checklist.^
12,13
^

**Fig. 1 f1:**

Participant randomisation for each 4-week arm.

### Patient and public involvement

In preparation of this protocol, two consumers from a community-based rehabilitation service living with schizophrenia were engaged to inform the proposed study design, including assessment measures. The consumers trialled both the meal kits and the pre-prepared meals and provided feedback on their experience, which was incorporated in the finalised protocol and study design.

### Setting and study population

Eighteen eligible participants, aged 18–64 years, will be recruited through public community mental health rehabilitation settings (Community Care Units) at Metro South Hospital and Health Services, Australia. Participants will complete all three study arms, per recommendations for participatory design and user testing activities.^
14
^

Consumers will be invited to participate in the study if they have a diagnosis of schizophrenia or schizoaffective disorder (DSM-5) and body mass index (BMI) ≥25 kg/m^2 15
^ at baseline, have had <5% body weight increase or loss in the previous 3 months and live in independent accommodation with access to a kitchen with relevant utensils and equipment. All participants must have capacity to consent, be able to follow the study instructions and procedures, and provide their informed consent.

Capacity will be determined by collaboration between the treating team and delegated research staff, in compliance with the National Health and Medical Research Council (NHMRC) National Statement on Ethical Conduct in Human Research.^
16
^ All research staff are experienced in assessing the capacity of people with severe mental illness to provide informed consent. Ability to provide informed consent will be overseen by the participant’s treating psychiatrist.

Consumers will be excluded from the study if they are experiencing acute psychiatric symptoms requiring immediate hospital admission, have obesity induced by another endocrinologic disorder (e.g. Cushing syndrome, untreated hypothyroidism), have had previous surgical treatment of obesity, have a current or prior history with risk of relapse of a severe eating disorder, have dietary allergies that preclude safe consumption of provided meals or foods, or are living with someone who prepares meals for them.

### Intervention procedures

The two dietary interventions will be: (a) pre-prepared meals (i.e. Lite n’ Easy) and (b) meal kits (i.e. EveryPlate box with meal ingredients and preparation and/or cooking instructions). These two interventions were chosen on the basis of a review of options for pre-prepared meals and meal kits available at the time in Australia, conducted by a dietitian, which was further discussed with the research team.

All participants will receive 15 min in-person general nutrition and food safety education by a nutritionist at baseline, including hard copy resources on how to safely store and prepare food, how to identify and follow ‘best before’ and ‘use by’ dates, and information on healthy meal options aligned with the Australian Dietary Guidelines (2013).^
17
^

The order of the three arms that each participant will receive will be determined using a computer-generated randomisation table by an independent biostatistician. The data analyst will be blinded to randomisation to avoid bias, but the rest of the research team will be unblinded. This will allow the research team to ensure the timing of the ordering (dietary interventions) is aligned with the participant randomisation arm.

#### Pre-prepared meals

Lite n’ Easy is a commercial company in Australia that produces and delivers pre-prepared meals. Lite n’ Easy was chosen owing to the diversity of frozen meal options, delivery capability, dietitian involvement in menu design, and access to comprehensive meal nutrition information, and because it is an existing National Disability Insurance Scheme (NDIS)-approved provider.

In Australia, the NDIS provides funding and support for people with a disability, including those with schizophrenia. In certain cases, where the illness (or disability) means planning meals and following multi-step instructions is troublesome, the NDIS may subsidise the delivery of pre-prepared meals for a period.

#### Meal kits

EveryPlate is a commercial company in Australia. EveryPlate was selected as it provided the simplest recipes (four-step recipes) using affordable, known ingredients with the least requirements for existing pantry items or complex equipment compared with other providers. Although not currently eligible as an NDIS-subsidised meal option, meal kits were chosen as they remove the complex steps of meal planning and grocery shopping while also supporting the development of basic cooking skills with step-by-step guides, making cooking with fresh ingredients a more viable option.

For each dietary intervention phase, participants will receive one meal daily, delivered weekly, for 4 weeks. A similar amount of kilojoules (kJ) will be provided per week by the meals, with Lite n’ Easy and EveryPlate meals approximately matched for kJ content (between 2600 and 2900 kJ per meal). Meal ordering will be conducted by a nutritionist and based on nutritional quality, ease of preparation (meal kits) and participant food preference. Participant food preferences, such as a preference for major protein sources (meat, poultry, seafood or vegetarian), cuisines and spices, will be collected at baseline, and participants will be encouraged to inform the research team if their food preferences change or are not appropriately reflected in the meal selection.

#### Control

Participants in the active control phase will receive a weekly $100 AUD supermarket voucher for 4 weeks. This was chosen to ensure study participant retention during the control arm and relatively equal monetary value in each arm so as not to influence the food security measure.

### Trial visits, assessments and outcome measures

Study visits and assessments will follow the schedule outlined in Table 1. The clinical measures will be undertaken by experienced mental health clinicians trained in administering the study measures and supervised by the research manager. Clinical measures will be administered at the participant’s choice of either the mental health clinic or their home residence.

**Table 1 tbl1:** Schedule of visits and assessments

Assessments														
Visit	0	1	2	3	4	5	6	7	8	9	10	11	12	13
	Screening	Baseline												
Week		0	1	2	3	4	5	6	7	8	9	10	11	12
Study period (12 weeks)														
Screening and consent														
Assessment of current medication	x	x	x	x	x	x	x	x	x	x	x	x	x	x
Informed consent	x													
Ongoing capacity	x	x	x	x	x	x	x	x	x	x	x	x	x	x
Inclusion and/or exclusion criteria	x													
Safety														
Adverse events		x	x	x	x	x	x	x	x	x	x	x	x	x
Clinical profiling														
Demographics (e.g. age, gender, indigenous status, marital status, education, employment)		x												
Medical history and medications (e.g. mental health conditions, physical health conditions, duration of illness)		x												
PANSS total		x												
Physical activity (SIMPAQ)		x												
Trail Making Test		x												
CVLT-III short form		x												
Rey Complex Figure Test		x												
Tower of London		x												
GAF		x												
Feasibility														
Food adherence^ a ^														
Meal adherence			x	x	x	x	x	x	x	x	x	x	x	x
Meal wastage			x	x	x	x	x	x	x	x	x	x	x	x
Meal preparation difficulty			x	x	x	x	x	x	x	x	x	x	x	x
Acceptability survey^ b ^					x				x					
Implementation of interventions (via semi-structured qualitative interview)						x				x				x
Efficacy														
Height		x												
Body weight (kg), BMI		x				x				x				x
Waist circumference and hip/waist ratio		x				x				x				x
Heart rate		x				x				x				x
Blood pressure		x				x				x				x
Dietary intake (24 h diet recall)		x			x				x				x	
Quality of life (SF-36)		x				x				x				x
Food insecurity (HFIAS)		x				x				x				x
Food knowledge, acquisition, and preparedness		x				x				x				x

BMI, body mass index; SF-36, Short Form Survey; HFIAS, Household Food Insecurity Access Scale; PANSS, Positive and Negative Syndrome Scale; SIMPAQ, Simple physical Activity Questionnaire; CVLT-III, California Verbal Learning Test 3rd Edition; GAF, Global Assessment of Functioning.

a Delivery of the two interventions and adherence to the instructions of both intervention options will not be completed for the control arm.

b The acceptability survey will not be completed for the control arm.

The measures relevant to the primary objective of the trial (i.e. assessment of feasibility and acceptability of two dietary interventions) will be collected through a checklist which participants will be requested to complete daily during the 4 weeks of each intervention arm and weekly for the control arm. To assist participants with completing the dietary checklists, research staff will send SMS reminders to participants and collect the checklists weekly.

This information will be complemented with data obtained from: (a) a semi-structured interview, conducted after participation in both dietary interventions and the control condition (week 12), asking participants about their views and experiences of each intervention; and (b) an acceptability survey, completed in week 3 to align with the 24-h diet recall visit.

### Outcome variables

#### Clinical profiling

The following measures will be conducted at baseline to establish a profile of the participant cohort and account for potentially confounding factors.Demographics and medical history: participant age, gender, indigenous status, marital status, education, employment, smoking status, current mental and physical health diagnosis, duration of illness, length of time spent in a mental health rehabilitation setting and current medications.Positive and Negative Symptom Scale: subscales including positive, negative and general psychopathology, a widely used scale for measuring symptom severity of people with schizophrenia.^
18
^
Simple Physical Activity Questionnaire: a five-item questionnaire developed as a clinical tool to assess physical activity and sedentary behaviour in people living with mental illness, using an interview format to provide a snapshot of a 24-h period estimate of time in bed, minutes of structured exercise participation, and incidental or non-structured physical activity.^
19
^
Trail Making Test: a neuropsychological test of attention, sequencing, cognitive flexibility, visual scanning, processing speed and motor function. The test can provide information about a person’s ability to alternate attention or shift mental set.^
20
^
California Verbal Learning Test brief form: a brief screening measure of episodic verbal learning and memory, which demonstrates sensitivity to a range of clinical conditions.^
21
^
Rey Complex Figure Test and Recognition Trial: captures information about five domains of neuropsychological functioning. Visuospatial recall memory and recognition memory are the primary reasons to give this measure.^
22
^
Tower of London: a neuropsychological measure of planning ability that is widely used in clinical and research contexts.^
23
^
Global Assessment of Function: a numeric scale (1 to 100) used by mental health clinicians and physicians to rate subjectively the social, occupational and psychological functioning of adults.^
24
^

#### Feasibility

Feasibility will be determined by self-reported: (a) meal adherence, (b) meal wastage and (c) meal preparation difficulty using a dietitian-designed daily checklist (Supplementary File 1 available at https://doi.org/10.1192/bjo.2025.10070) to record consumption of pre-prepared meals or meal kits as intended.

#### Acceptability

Acceptability will be determined by recruitment rate and retention, completion of the acceptability survey and semi-structured qualitative interviews. The acceptability survey will determine the participants’ perceived acceptability of each meal intervention using a nine-item, five-point Likert scale survey (Supplementary File 2), with each item aligned with a validated construct of acceptability from the Theoretical Framework of Acceptability.^
25
^ In addition, the participant will be given an opportunity to provide a short open-ended clarification for each score. The semi-structured interviews will explore participant experience of and preference for each intervention, questions informed by the Acceptability of Intervention Measure, Intervention Appropriateness Measure, and Feasibility of Intervention Measure.^
26
^ In addition, participants will be asked to rank all three arms of the study in order of preference.

#### Efficacy

Secondary outcome measures (i.e. exploration of the preliminary efficacy of two dietary interventions) will be assessed at the start (baseline) and at the end of each 4-week block, except for dietary intake, which will be assessed at baseline and week 3 of each arm (a time frame chosen to reduce participant burden in week 4). Exploratory efficacy will be evaluated using the following measures.

Physical health measures: weight will be recorded to the nearest 0.1 kg with calibrated Ade M322600 portable scales, with the same pair of scales used throughout the trial. Height, without shoes, will be measured using a tape measure mounted on the wall, with an accuracy of 0.1 cm. BMI will be calculated as weight (kg)/height (m^2^). Waist circumference will be measured halfway between the lower border of the ribs and the iliac crest in a horizontal plane. Hip circumference will be measured around the widest portion of the buttocks in a horizontal plane. Both measures will be to the nearest 0.5 cm using a non-stretchable measuring tape. Participants will be asked to remove belts or garments that may change the shape of their bodies. Where possible, the same research staff will take measurements for a participant at baseline and follow-up time points for consistency. Waist-to-hip ratio will be calculated as waist circumference (cm) divided by hip circumference (cm). Systolic and diastolic blood pressure will be measured manually at all visits using an EliteCare Traditional Sphygmomanometer (accuracy: 0.5 mm Hg) on the left arm while sitting. Participants will be asked to avoid caffeine, smoking and physical activity for 30 min before the measurements. Pulse will be recorded after 5 min of seated rest.

24-h multi-pass dietary recall: a five-phase face-to-face assessment of dietary intake conducted by a nutritionist or dietitian. The participant is guided to iteratively provide detail about each food and drink consumed within the previous 24-h period (modelled on the US Department of Agriculture’s Automated Multi-Pass Method.^
27
^). The 24-h recall will be entered into FoodWorks Online Professional (version 2, Xyris, Brisbane, Australia) for nutritional analysis including energy, macronutrient, sodium, and core and discretionary food group intake.

Short Form 36 Health Survey: a self-rated survey, validated for people with schizophrenia,^
28
^ measuring overall quality of life and covering general health, activity level, and emotional and somatic complaints with associated disability. The measure produces two component scores: the physical component summary and mental component summary. A high score represents a more favourable health state; the lowest and highest possible scores are 0 and 100, respectively.^
29
^

Household Food Insecurity Access Scale (HFIAS): a nine-question food security measurement tool, assessing feelings or behaviour around food anxiety, food quality and food quantity over the previous 30 days.^
30
^ The HFIAS has been used in several countries and appears to distinguish food-insecure from food-secure households across different cultural contexts. The information generated by the HFIAS can be used to assess the prevalence of household food insecurity (access component) and to detect changes in the food insecurity situation of a population over time.^
31
^

Food knowledge, acquisition and preparedness: a self-administered quantitative questionnaire will be used to assess cooking confidence (self-efficacy) and cooking and eating behaviours. Cooking confidence (self-efficacy) is evaluated using five questions that assess participants’ confidence in cooking skills necessary for basic home cooking. These skills are rated on a scale from 1 to 5, with 1 representing ‘not at all confident’ and 5 indicating ‘extremely confident’. An overall confidence score is calculated by summing the individual item scores.

Cooking and eating behaviours will be evaluated using six questions. Frequency of cooking the main meal from basic ingredients, frequency of eating ready-made meals, and frequency of eating vegetables with the main meal are measured on a scale from 0 (never) to 7 (daily); daily vegetable intake is measured on a scale from 0 (no servings per day) to 6 (six or more servings per day); and number of servings of fruit per day and frequency of eating takeaway meals are measured from 0 (never) to 5 (five or more times per week).^
32
^

### Data management

Data will be collected and stored according to *Good Clinical Practice*. A screening log will be used to track potential participants, consent, eligibility, withdrawals and completion as per the Consolidated Standards of Reporting Trials requirements.^
33
^ De-identified, hard copy case report forms (CRF) with questionnaires and clinical data will be stored securely at the research team site. CRF data will be entered into REDCap, a secure web-based application, and exported into statistical analyses software (IBM SPSS version 29).

Owing to this being a pilot trial, no data management committee is required. All adverse events and serious adverse event data will be reported to all study investigators, who will jointly decide whether a stopping procedure should be instigated.

### Data analyses

Basic tabular descriptive statistics will include sample size for each group, range of scores, means, standard deviations and coefficient of variations for continuous variables with reasonably symmetrical distributions, or median and interquartile range for highly skewed variables. Differences in baseline mean symptom severity (measured with the Positive and Negative Symptom Scale and Global Assessment of Function) will be assessed across the three groups using unstandardised mean differences.

Primary outcome measures will be assessed against predetermined criteria for feasibility and acceptability as listed in Table 2. Primary and secondary outcomes will be assessed using *t*-tests and Mann–Whitney *U*-test for continuous variables. Categorical variables will be assessed using chi-squared tests by comparing the baseline scores for all participants randomised to one arm with end-point scores (at week 4) of all participants for that arm and in the same way for the other two study arms. This within-intervention analysis will then be extended to compare the same outcomes across the three arms using analysis of variance. Potential confounders such as gender, age, physical comorbidities and BMI will be considered.

**Table 2 tbl2:** Primary outcome measures and criteria for success

Feasibility	Intervention	Data	Collection method	Success criteria
Meal adherence	Pre-prepared meals	Proportion of pre-prepared meal eaten.	Checklist	Half or more of the meal was eaten ≥80% of the days.
	Meal kit	Did you follow the recipe? Did you split the recipe into two servings? Did you eat the prescribed portion of the meal kit meal today?	Checklist	Recipe followed at least 50% of time (six of 12 recipes). Of recipes attempted, food split into two meal servings 100% of time. Half or more of the meal serving was eaten ≥80% of the days.
	Control	Proportion of voucher spent on food?	Checklist	3 of 4 weeks ‘all’ voucher spent on food.
Meal wastage	Pre-prepared meals	If prepared meals were uneaten,– what happened to leftovers?	Checklist	Of meals prepared, some or all food ‘went in bin/remained uneaten’ <25% of the time.
	Meal kit	If recipe not followed what happened to unused ingredients?	Checklist	For each kit, unused ingredients went in the bin or remained uneaten ≤1 time.
		If unused ingredients at end of week, what happened to them?	Checklist	For each kit, unused ingredients went in the bin or remained uneaten ≤1 time.

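### Mann–Whitney U and chi-squared tests are assigned to cross-over data in which the same 18 people supply every arm, and the t-tests and ANOVA are not fixed as within-participant

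*Protocol article*

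**What the plan says.** The design is stated without ambiguity. The Abstract (Method) has participants "crossing-over at the end of weeks 4 and 8, so that all participants experience all three study arms". Setting and study population repeats it ("Participants will complete all three study arms") and gives the sample size: "Eighteen eligible participants, aged 18–64 years, will be recruited". Under Efficacy, secondary outcomes are measured at week 0 and at the end of each four-week block, with dietary intake taken at baseline and in week 3 of each arm.

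The Data analyses section then names these methods:

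- Continuous outcomes: "Primary and secondary outcomes will be assessed using *t*-tests and Mann–Whitney *U*-test for continuous variables".
- Categorical outcomes: chi-squared tests that set the baseline of an arm's participants against the end-point of the participants in that arm.
- Between arms: this analysis is extended to "compare the same outcomes across the three arms using analysis of variance".
- Adjustment: "Potential confounders such as gender, age, physical comorbidities and BMI will be considered".
- Baseline symptom severity (PANSS and GAF): differences "will be assessed across the three groups using unstandardised mean differences".

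No paired, signed-rank, McNemar, Friedman, repeated-measures or mixed-model method is named.

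**The concern.** In a cross-over each person acts as their own control. The gain in precision comes from removing stable between-person differences from the error term. Mann–Whitney U and chi-squared cannot do this, because they treat the two sets of values as coming from different people. Neither has a paired form: the paired counterparts are different tests with different names.

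If the section is followed as written, between-person variation stays in the error. Confidence intervals are then too wide and p-values too large, and real within-person differences are likely to be reported as no difference. With 18 people, much of the value of the preliminary efficacy data rests on the precision that this gives away.

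**Working it through.** **Is there a figure to reproduce?** No. The article gives no significance level, power, effect size, standard deviation or within-person correlation, and the 18 comes without a calculation.

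**Inputs.** From the article: n = 18, each person in all three arms. Assumed: two-sided 5% level, ρ from 0.3 to 0.8, normal data with equal variances, no dropout, no period or carry-over effect. Results are in units of the between-person standard deviation (SD).

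**Formulas.**

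- Arms treated as independent: SE = √(2/n) = √(2/18) = 0.333, whatever ρ is.
- Within-person: SE = √(2(1−ρ)/n). At ρ = 0.5 this is √(2 × 0.5/18) = 0.236.
- Ratio: 1/√(1−ρ).
- 95% interval half-width: 2.03 × 0.333 = 0.68 with 34 degrees of freedom if independent; 2.11 × SE with 17 degrees of freedom if paired.
- Detectable difference: 80% power from the noncentral t distribution.

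| | ρ = 0.3 | ρ = 0.5 | ρ = 0.8 |
|---|---|---|---|
| SE, independent | 0.333 | 0.333 | 0.333 |
| SE, paired | 0.279 | 0.236 | 0.149 |
| Overstatement of SE | 1.20 | 1.41 | 2.24 |
| Half-width, independent | 0.68 | 0.68 | 0.68 |
| Half-width, paired | 0.59 | 0.50 | 0.31 |
| Detectable difference, independent | 0.96 | 0.96 | 0.96 |
| Detectable difference, paired | 0.83 | 0.70 | 0.44 |

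**Simulation** (20,000 trials; 4,000 for Mann–Whitney), nominal level 5%:

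| | ρ = 0.3 | ρ = 0.5 | ρ = 0.8 |
|---|---|---|---|
| True type I error, Mann–Whitney | 2.2% | 0.7% | <0.1% |
| True type I error, one-way ANOVA | 1.5% | 0.4% | <0.1% |
| Power for 0.5 SD, Mann–Whitney | 24.5% | 23% | 17% |
| Power for 0.5 SD, paired t | 39% | 52% | 89% |
| Power for 0.5 SD in one arm, one-way ANOVA | 25% | 20% | 11% |
| Power for 0.5 SD in one arm, repeated-measures ANOVA | 41% | 55% | 93% |

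The paired t-test and the repeated-measures ANOVA kept type I error at about 5% throughout. For a binary outcome with a true proportion of 0.5, the chi-squared test rejected a true null in 2.3% of trials at a latent correlation of 0.5 and in 0.4% at 0.8. The one-way ANOVA rows apply only if the unspecified ANOVA is run that way.

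**Which outcomes are affected?** Table 1 collects weight, waist, blood pressure, quality of life and food insecurity at weeks 0, 4, 8 and 12. Both the pre–post and the between-arm comparisons of these are within-person. Meal adherence, wastage and preparation difficulty start in week 1 and have no baseline, so only their between-arm comparison is concerned. The acceptability survey is not done in the control arm, so it can contribute only a two-arm comparison.

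**The case against.** The strongest reply is that a condensed article need not give the form of every test. The words used for t-tests and analysis of variance are compatible with paired t-tests and repeated-measures ANOVA, and the section itself calls the pre–post comparison within-intervention. This stands for those two methods: the fault there is only that the form is not fixed. Likewise, the silence on period and sequence terms is something an analysis plan may fill, and is not an error in itself. The reply does not reach Mann–Whitney U and chi-squared, which are named outright and have no within-person form.

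A second reply concerns the parenthesis that places the end-point at week 4. If it means the first period only, the arms are different people and independent-groups tests are valid between arms. But the pre–post comparison is still made in the same people. About 6 per arm would remain, with a detectable between-arm difference of about 1.8 SD, so the precision of the cross-over is lost on that reading too.

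Three stronger inferences are tempting but not supported:

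- *That the baseline comparison of PANSS and GAF is zero by construction.* This is so only if the three groups are the three arms with complete follow-up. The phrase can also mean groups by first allocated arm, who are different people.
- *That the listed confounders can play no part.* They are participant traits and largely cancel within a person, but BMI is re-measured at each block and incomplete follow-up would disturb the balance.
- *That the trial's main conclusions are at risk.* Primary outcomes are judged against the descriptive criteria in Table 2, and Limitations concedes that the pilot is not powered for efficacy.

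**Conclusion.** The point holds for Mann–Whitney U and chi-squared as wrongly named methods, and for the t-tests and ANOVA as methods whose form is left open. Independent-groups analysis overstates the SE by a factor of 1.20 to 2.24 for ρ between 0.3 and 0.8. The correlation is an assumption and will differ by outcome. At ρ = 0 there is nothing to gain: the detectable difference would be 0.99 SD paired against 0.96 SD independent.

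With positive within-person correlation the error runs one way. It hides differences and does not create false positives, so a reader should not infer that spurious effects will be reported. The harm falls mainly on the secondary efficacy outcomes. This should be fixed before analysis, but it does not undermine the feasibility and acceptability decisions.

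**What to change.** Amend the Data analyses section as follows:

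- Replace Mann–Whitney U with the Wilcoxon signed-rank test for two-way comparisons and Friedman's test across three arms.
- Replace chi-squared with McNemar's test for two paired proportions and Cochran's Q for three.
- State that t-tests are paired.
- State that the comparison across arms is within-participant, preferably a linear mixed model with a random participant effect and fixed arm and period effects, reporting arm differences with 95% confidence intervals. A repeated-measures ANOVA would also answer the main point; the mixed model is a preference.
- Describe baseline PANSS and GAF for the whole cohort, or by randomised sequence, instead of across three groups.

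The cost is wording only. The measurements are already scheduled, and SPSS version 29, named under Data management, fits mixed models. No participants, visits or data are added.
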